## Abstract

*Background*. Chinese herbal medicine (CHM) has been used in the treatment of chronic heart failure (CHF) for a long time. Treatment based on syndrome differentiation and the main characteristic of TCM is the fundamental principle of TCM practice. In this study protocol, we have designed a trial to assess the efficacy and safety of CHM on CHF based on syndrome differentiation. *Methods/Design*. This is a three-stage trial of CHM in the treatment of CHF. The first stage is a literature review aiming to explore the common syndromes of CHF. The second is a multicentral, randomized, placebo-controlled trial to evaluate the efficacy and safety of CHM for the treatment of CHF. The third is a multicentral, randomized controlled clinical trial aiming to make cost-effectiveness analysis and evaluate the feasibility, compliance, and universality of CHM on CHF. *Discussion*. This trial will evaluate the efficacy, safety, feasibility, compliance, and universality of CHM on CHF. The expected outcome is to provide evidence-based recommendations for CHM on CHF and develop a prescription of CHM in the treatment of CHF. This trial is registered with NCT01939236 (Stage Two of the whole trial).

## 1. Background

Heart failure, as the final stage of cardiac diseases, is an abnormality of cardiac structure or function. This would lead to the failure of the heart to deliver oxygen at a rate commensurate with the requirements of the metabolizing tissues, despite the normal filling pressures or increased filling pressures [1]. In addition, according to the character of the clinical manifestation, HF is divided into acute and chronic HF. In 2003, a random sample survey of 15,518 urban or rural residents from 35 to 74 years old was made in China: the prevalence rate of heart failure was 0.9%, and according to the result there were approximately 4 million HF targets in China [2]. The diagnosis and treatment of cardiovascular disease (CVD) have developed quickly in the past several decades. The mortality of CVD has fallen down, except for HF. Annual hospital discharge in subjects with a primary diagnosis of HF has been rising steadily since 1975. And now it has exceeded 1 million discharges per year, though they may at last be leveling off in the United States [3, 4]. It can be expected that the incidence of HF in China will be in a significantly increasing trend, and the number of CHF patients will increase in the future.

According to the guideline, the conventional therapeutic approaches in HF management are angiotensin-converting enzyme inhibitors (ACEIs), *β*-adrenergic blockers, and diuretics [5]. However, side effects, such as electrolyte, fluid depletion, and hypotension, are common during the treatment with western medicine [6]. Therefore, CHM, as an alternative medicine, has been considered the treatment of CHF with lower cost and fewer side effects.

In China, CHM has been used in the treatment of diseases for thousands of years. Treatment based on syndrome differentiation is the main characteristic and therapeutic rule of TCM. Syndrome differentiation is the comprehensive analysis of the clinical information gained by the four main diagnostic TCM procedures—observation, listening, interrogation, and pulse-taking, and it is used to guide the choice of treatment by CHM. Many clinical studies [7–9] have shown the efficacy of CHM on CHF. But in these studies, the syndrome of the CHF patients was stationary, and the formulation of CHM was in the form of capsule or injection. They may not completely reflect the efficacy of CHM in the treatment of CHF based on syndrome differentiation. This trial aims to evaluate the efficacy and safety of CHM in the treatment of CHF based on syndrome differentiation.

## 2. Objectives

The objective of this trial is to assess the efficacy and safety of CHM on CHF based on syndrome differentiation and to develop a prescription of CHM in the treatment of CHF which could be generally used in community health service centers.

## 3. Methods 

### 3.1. Design

This is a three-stage, multicentral clinical trial in the treatment of CHF. The first stage is a literature study and aims to explore the common syndromes of CHF. The second stage is a multicentral, randomized controlled clinical trial with double-blinded method and aims to evaluate the efficacy and safety of CHM based on syndrome differentiation. The third stage is a multicentral, randomized controlled clinical trial and aims to make cost-effectiveness analysis and evaluate the feasibility, compliance, and universality of CHM on CHF based on syndrome differentiation.

#### 3.1.1. Stage One

The first stage was to analyze the most common syndromes of CHF. A flowchart of Stage One is shown in Figure 1.

*Inclusion Criteria for the Literature*. The literatures included should focus on clinical research of CHM or integrative medicine on CHF.

The literatures should have integral data with exact data information about CHF syndromes. 

*Exclusion Criteria for the Literature*. If the content of articles was identical and the study was identified to be the same one, we select one article with the most complete information: literature reviews, case reports, export advice, the literature focusing on the analysis of pathogenesis or the syndromes substantive, the source of the literature being unknown or the actual situation being clearly incompatible with the clinical literature.

*Search Range for Articles*. We searched the China National Knowledge Infrastructure Database (CNKI), the China Biology Medicine Database (CBM), and the Chinese Science and Technology Periodical Database (VIP) from January 1994 to January 2008. Databases search strategies are shown in Table 1. 

*Search Methods*. The literature search work was carried out by 2 students independently in the same search terms. After all work was accomplished, we checked the search result and resolved the differences through discussion. If the disagreements still could not be resolved, we invited related experts for identification. 

*Selecting the Content of Related Literatures*. We selected records of CHF and syndromes and related information. 

*The Processing Methods of Selected Records*. We picked out TCM syndromes, symptoms, and signs in records and attached the related information, such as paper title, journal name, issue number, page count, and author.

All data were input into database established with Epidata 3.0. The frequency of common syndromes and symptoms was analyzed. We encoded these common syndromes and symptoms and regulated the related TCM terms. We unified the TCM names or aliases with the same meaning but different expression into uniform names. 

*Summarizing and Classifying the Findings of Literatures*. We summarized the clinical characteristics and distribution of CHF common syndromes from the results of searched records. There were 1432 literatures with full text search in three databases. According to inclusion and exclusion criteria, we selected 176 literatures from the three literature databases. According to Clinical Terminology of Diagnosis and Treatment for Traditional Chinese Medicine—Syndrome Section and Pharmacy Terminology of Traditional Chinese Medicine, with the suggestion of experts, we standardized all symptoms and syndromes of CHF. There were twelve symptoms with more than 100 repetitions after standardization, which were shown in Table 2. The top six symptoms are yang deficiency, qi deficiency, blood stasis, water retention, yin deficiency, and turbid phlegm, which were shown in Table 3 [10]. Combined with the literature review and experts' suggestions, we decided to make qi deficiency, blood stasis, yang deficiency, and water retention as objects for the further trial of Stages Two and Three.

#### 3.1.2. Stage Two

The second stage of this trial was a multicentral, randomized clinical trial with placebo-controlled and double-blind methods.  Figure 2 shows the trial flowchart. 

*Diagnostic Criteria*

*Diagnostic Criteria for CHF*. Diagnostic criteria were as follows: (1) diagnostic criteria of CHF:* 2007 China Guideline for the Diagnosis and Treatment of CHF* [5]; (2) heart function standard:* The Criteria for Diagnosis and Treatment of Heart Disease *first published by the New York Heart Association (NYHA) [11]. 

*Diagnostic Criteria for TCM Syndrome Differentiation*. Diagnostic criteria were as follows: TCM differentiation standard: according to the* Guiding Principles for the Clinical Study of New Drugs in Traditional Chinese Medicine* released in 2002 [12]. 

*Inclusion Criteria for Participants*. Patients who accorded with diagnostic criteria were potentially eligible for the study if they met the following criteria.The primary heart disease is CHD (with diagnosis for CHD confirmed by coronary angiography, coronary computed tomography, history of acute myocardial infarction, limb-salvage Q wave for electrocardiogram (ECG), ECG test, radionuclide examination support, etc.). The included patients should have no history of hypertension or taking antihypertensive drugs, with a blood pressure under 160/100 mmHg.With a history of CHD, the following symptoms and signs were observed: difficult breathing, fatigue, fluid retention (edema), left ventricular enlargement, systolic volume of left ventricular increase with LVEF ≤ 40%, and NYHA functional classification II or III.Male or female patients should be between 40 and 75 years old.If there was any violation of those criteria, the subject could not participate in this research.

*Exclusion Criteria for Participants*. Patients would be excluded if they met one of the following criteria.Patients with one of the following diseases: (1) acute valvular heart disease; (2) pericardial disease; (3) cardiomyopathy; (4) congenital heart disease; (5) acute myocardial infarction (AMI) within four weeks; (6) cardiac shock; (7) acute myocarditis or serious arrhythmia with variation in hemodynamics.Patients who suffer from pulmonary artery hypertension caused by cor pulmonale, pulmonary embolism, or stroke within a half year.Patients who suffer from serious hepatic insufficiency (the index of liver function being 2 times the normal one), renal insufficiency (Ccr > 20%, Scr > 3 mg/dL, or 265 *μ*mol/L), diseases of blood system, malignant tumor, diabetes mellitus with serious complications, hyperthyrea, or hypothyrea.Patients who suffer from infection, fever, or patients meeting one of the following criteria: the numeration of leukocyte being more than 10 × 10^9^/L, the percentage of neutrophil granulocyte being more than 85%; patchy shadows in X-ray of chest.Pregnant women and women in lactation.Patients with mental disorders or related infections.Patients who took part in other trials within two months before the present study.

*Sample Size*. The sample size calculation is based on prophase clinical study (31 cases, 13 in CHM group and 18 in placebo group), standard deviation of experimental group (*S*
_*e*_) = 25.84718, standard deviation of control group (*S*
_*c*_) = 32.54499, mean of experimental group (${\bar{x}}_{e}$) = 39.07692, mean of control group (${\bar{x}}_{c}$) = 32.54499, and the number of control group (*c*) = 1. The following formula is used to calculate the sample size:(1)$$\begin{array}{c} n=\frac{{\left(\upsilon_{\alpha }+\upsilon_{\beta }\right)}^{2}\left(1+1/c\right)\sigma^{2}}{\delta^{2}}\\ \sigma^{2}=S^{2}=\frac{S_{e}^{2}+cS_{c}^{2}}{1+c}\delta^{2}={\left|{\bar{x}}_{e}-{\bar{x}}_{c}\right|}^{2}. \end{array}$$

The estimated number of subjects in each group was 98.18012, and 196.36024 subjects are needed in two groups. The number was increased to 215.18012 assuming a maximum dropout rate of less than or equal to 10%, and a total of 220 subjects were included (110 subjects in each group).

*Randomization*. A total number of 220 participants were randomly assigned with a ratio of 1 : 1 to CHM or placebo group according to random number sequence. Stratified blocked randomization was taken to insure the balance of two groups.

*Blinding*. In this stage, the double-blind design was used. Drugs for CHM and placebo groups were prepared and provided by Beijing Kangren Tang Pharmaceutical Co., Ltd. (Beijing, China). In CHM group, drugs of four syndromes (qi deficiency, blood stasis, water retention, and yang deficiency) were prepared, while the placebo was provided in the same character, smell, and weight as the drugs for CHM group. Drugs of each syndrome were prepared as granules without decoction. The CHM drugs and placebo were numbered according to a random figure table which was blinded to both the doctors and the patients. Participants were provided with CHM or placebo based on their syndrome differentiation at the beginning and two weeks later. They took CHM or placebo twice per day for four weeks.

*Setting*. In this stage, participants were admitted into seven hospitals of four provinces in China: (1) Dongfang Hospital Affiliated to Beijing University of Chinese Medicine; (2) The Affiliated Hospital to Changchun University of TCM; (3) Guang'anmen Hospital Affiliated to China Academy of Chinese Medicine Sciences; (4) Hubei Provincial Hospital of TCM; (5) Wuhan Hospital of TCM; (6) Yichang Hospital of TCM; (7) Zhengzhou Hospital of TCM.

*Interventions*. According to the guideline for chronic heart failure [5], standardized western medicine treatment, such as angiotensin-converting enzyme inhibitors (ACEIs) or angiotensin-receptor blockers (ARBs), *β*-blockers, and diuretics, could be used for patients in CHM and placebo groups as basic therapy. The dosages of all medicines used are following the guideline for CHF [5].

The recipe for qi deficiency was composed of* Astragalus membranaceus* (Fisch.) Bge. var.* mongholicus *(Bge.) Hsiao (huangqi, 60 g) and* Codonopsis pilosula *(Franch.) Nannf. (dangshen, 15 g).

The recipe for blood stasis was composed of* Salvia miltiorrhiza *Bge. (danshen, 15 g),* Paeonia lactiflora *Pall. (chishao, 15 g),* Prunus davidiana* (Carr.) Franch. (taoren, 10 g), and* Carthamus tinctorius* L (honghua, 10 g).

The recipe for water retention was composed of* Alisma orientalis *(Sam.) Juzep. (zexie, 10 g),* Polyporus umbellatus* (Pers.) Fries (zhuling, 15 g),* Plantago asiatica* L. (cheqianzi, 10 g), and* Descurainia sophia *(L.) Webb. ex Prantl (tinglizi, 10 g).

The recipe for yang deficiency was composed of* Cinnamomum cassia *Presl (rougui, 4.5 g) and* Aconitum carmichaelii *Debx. (zhifuzi, 10 g).

Table 6 lists the names of the CHM drugs in Chinese and English. All CHM herbs were verified by high-performance liquid chromatography (HPLC).

Patients in placebo group received placebo which was the same in shape, size, taste, weight, and package as CHM granules. CHM drugs and placebo were prepared as granules. Granules quality met internal control standards of Beijing Kangren Tang Pharmaceutical Co., Ltd. (Beijing, China), and complied with GMP (Good Manufacturing Practice) standards. Patients were treated with CHM or placebo granules twice per day for four weeks based on syndrome differentiation.

Participants were prohibited from taking other Chinese medicine during the treatment period.

The drugs for the treatment of hypertension (HBP), diabetes mellitus, dyslipidemia, and other diseases could be used reasonably. And the reason, name, and dosage should be recorded in detail.

*Outcome Measurements*. The primary outcome measure was left ventricular ejection fraction (LVEF). Secondary outcome measurements were 6-minute walk test (6MWT), traditional Chinese medicine syndrome scores, and New York Heart Association (NYHA) functional classification. Side effects were to be monitored during the trial period. Many biological indicators (blood routine examination, liver function, kidney function, and ECG) were tested before and after the treatment. The timeline of participants through Stage Two is shown in Table 4.

*Statistical Analysis*. Data were analyzed on the Intention-to-Treat (ITT) analysis and the per-protocol set (PPS) for coherence. The basic characteristics were compared with independent samples *t*-test for continuous variables and chi-square analyses for categorical variables. Repeated-measure ANOVA was used for the evaluation of the primary and secondary outcomes. The measurement data were expressed as mean ± standard deviation for us to check the data of all groups with normal test and homogeneity of variance test. Results were shown with 95% confidence intervals (CIs). The level of significance was set at 0.05. If *P* < 0.05, there were statistical differences. All tests were 2-tailed.

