#### 3.1.3. Stage Three

If the efficacy of CHM on CHF is better than placebo in Stage Two, we will conduct Stage Three to evaluate the feasibility, compliance, and universality and make cost-effectiveness analysis of CHM on CHF based on syndrome differentiation. A flowchart of the third stage is shown in Figure 3.

*Diagnostic Criteria*

*Diagnostic Criteria for CHF*. Diagnostic criteria are the same as those of Stage Two.

*Diagnostic Criteria for TCM Syndrome Differentiation*. Diagnostic criteria were the same as those of Stage Two.

*Inclusion Criteria for Participants*. Patients who accorded with diagnostic criteria were potentially eligible for the study if they met the following criteria.The primary heart disease is CHD (with diagnosis for CHD confirmed by coronary angiography, coronary computed tomography, history of acute myocardial infarction, limb-salvage Q wave for electrocardiogram (ECG), ECG test, radionuclide examination support, etc.). The included patients also had no history of hypertension or taking antihypertensive drugs, with a blood pressure under 160/100 mmHg.With a history of CHD, the following symptoms and signs were observed: difficult breathing, fatigue, and fluid retention (edema), with left ventricular enlargement, along with increasing of left ventricular end systolic volume and LVEF ≤ 50%, with NYHA cardiac function II or III.Male or female patients should be between 40 and 75 years old.

If there is any violation of those criteria, the subject could not participate into this research.

*Exclusion Criteria for Participants*. Exclusion criteria were the same as those in Stage Two.

*Sample Size*. This design in this stage is to show the superiority of TCM based on syndrome differentiation. The ratio in this stage is 1 : 1. The sample size calculation is based on LVEF of Stage Two. To calculate the sample size, we will use the following formula (*δ* = 2):(2)$$\begin{array}{c} n=\frac{\left({\left(Z_{1-a/2}+Z_{1-\beta }\right)}^{2}*\left(\sigma_{1}^{2}+\sigma_{2}^{2}\right)\right)}{{\left(\varepsilon -\delta \right)}^{2}}. \end{array}$$

And the maximum dropout is 10%.

*Randomization*. All participants in this stage will be randomly distributed to CHM or placebo group according to random number sequence.

*Setting*. In this stage, five or more centers will take part in the trial.

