*Interventions*. Besides standardized western medicine treatment, participants in CHM group will receive CHM based on syndrome differentiation. Control Group will receive standardized western medicine only.

CHM granules will be prepared as in Stage Two.

*Outcome Measurements*. In this stage, the primary outcome measurement is LVEF. Secondary outcome measurements are 6MWT, TCM syndrome scores, and NYHA functional classification. Meanwhile, the feasibility, cost-effectiveness analysis, compliance, and universality will be evaluated or performed. Feasibility and universality investigation of this research will be executed by the questionnaire of doctors and patients; compliance evaluation will be executed by the ratio between the actual amount of medication and the supposed amount in CHM group; cost effectiveness will be conducted by the ratio between the different improved condition of LVEF and treatment costs. Side effects will be monitored during the trial period. Biological indicators (blood routine examination, liver function, kidney function, and ECG) will be tested before and after the treatment. The timeline of participants through Stage Three is shown in Table 5.

*Statistical Analysis*. Data will be analyzed on the Intention-to-Treat (ITT) analysis and the per-protocol set (PPS) for coherence. The basic characteristics will be compared with independent samples *t*-test for continuous variables and chi-square analyses for categorical variables. The measurement data will be expressed as mean ± standard deviation for us to check the data of all groups with normal test and variance homogeneity test. The changes in measurement data between baseline and the assessment for four weeks will be performed with independent samples *t*-test. The categorical variables will be compared with chi-square analyses. Safety analysis will be conducted. Results will be shown with 95% confidence intervals (CIs). The level of significance will be set at 0.05. If *P* < 0.05, there will be statistical differences. All tests will be 2-tailed.

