### 3.3. Quality Control of Stages Two and Three

Research workbook will be formulated. Before the beginning of this stage, all investigators will be trained and tested according to conformance standard. Drugs in this trial will be identified by pharmaceutical manufacturing sector and prepared in accordance with national technical standards procedures. Drugs will be marked only for clinical trial, which cannot be sold. The investigators in clinical centers will take charge of the usage of drugs. The usage record of drugs should include the following information: quantity, shipment, delivery, acceptance, distribution, recycling, and destruction.

In order to achieve the same detection methods, the physicians for 6MWT evaluation and echocardiography will be trained together. Clinical research associates will test the research progress of all clinical centers.

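### The renal exclusion prints its creatinine-clearance cut-off in the opposite direction to its creatinine cut-off, with an undefined percent unit, and Stage Three inherits the line

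*Protocol article*

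**What the plan says.** Section 3.1.2 (Stage Two, Exclusion Criteria for Participants) opens with "Patients would be excluded if they met one of the following criteria". Within the criterion on liver, kidney and other diseases, it gives "renal insufficiency (Ccr > 20%, Scr > 3 mg/dL" and then restates the creatinine limit as 265 μmol/L. A comma separates the clearance part from the creatinine part. The only written connective in the bracket joins the two units of creatinine. Ccr is not in the abbreviation list, and nothing elsewhere in the article restates or corrects the line.

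Section 3.1.3 (Stage Three) takes the criteria over without change: "Exclusion criteria were the same as those in Stage Two". Both stages measure kidney function as a safety item. Stage Two has "Many biological indicators (blood routine examination, liver function, kidney function, and ECG) were tested before and after the treatment" and Stage Three has "Biological indicators (blood routine examination, liver function, kidney function, and ECG) will be tested before and after the treatment".

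**The concern.** One bracket is meant to describe one condition, renal insufficiency. High creatinine marks poor kidney function, while high clearance marks good function. Read as a level, a clearance above 20 is therefore not a sign of renal insufficiency, and the two parts pull in opposite directions. The percent sign adds a second ambiguity: it could mean percent of a normal value, it could stand for mL/min, or a word such as decline could be missing.

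What is at stake is safety screening. The line is an operative entry threshold in a trial that tests kidney function before and after treatment. The article describes Stage Two as finished and Stage Three as still to start, so the line can be put right before it is used again.

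**Working it through.** **1. The article's own figure.** With the usual conversion factor of 88.4, 3 mg/dL × 88.4 = 265.2 μmol/L, which matches the printed 265. The creatinine part is consistent in unit, and its direction is right for renal insufficiency. The clearance part is therefore the one at fault.

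**2. The rule under each connective.** Clearance (Ccr) is taken as a level in whatever unit, and creatinine (Scr) is in mg/dL.

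| Rule | Excluded | Left eligible |
|---|---|---|
| Printed, joined by or | Ccr > 20 or Scr > 3 | Ccr ≤ 20 and Scr ≤ 3 |
| Printed, joined by and | Ccr > 20 and Scr > 3 | everyone with Scr ≤ 3, plus those with Scr > 3 and Ccr ≤ 20 |
| Sign reversed, joined by or | Ccr < 20 or Scr > 3 | Ccr ≥ 20 and Scr ≤ 3 |

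- With or, the printed rule and the sign-reversed rule leave eligible groups that meet only at Ccr exactly 20. This needs no clearance formula, but it depends on the or and on reading Ccr as a level.
- With and, no patient with normal kidneys is excluded, but patients with both high creatinine and very low clearance pass the screen.
- If a word such as decline is missing, the sign and the percent both make sense. The criterion then lacks a baseline and a time frame, so it is undefined.

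None of the three readings gives a usable rule.

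**3. Illustration of direction under or.** The documents give no weights and no clearance formula, so these are assumptions: Cockcroft-Gault, Ccr = (140 − age) × kg / (72 × Scr), times 0.85 for women, with weights of 45 to 80 kg. Ages 40 to 75 come from the inclusion criteria.

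- At Scr 1.0 the highest value is 100 × 80 / 72 = 111.1 mL/min (man, 40 years, 80 kg). The lowest is 65 × 45 × 0.85 / 72 = 34.5 mL/min (woman, 75 years, 45 kg). All exceed 20 and would be excluded as printed.
- If the 20% means 20% of an assumed normal 80, 100 or 120 mL/min, the cut-off is 16, 20 or 24 mL/min. The smallest, oldest case reaches it at Scr 34.53 / 16 = 2.16, 34.53 / 20 = 1.73 or 34.53 / 24 = 1.44 mg/dL.
- At Scr 1.4 mg/dL (1.4 × 88.4 = 124 μmol/L) the lowest clearance in the range is 34.53 / 1.4 = 24.7 mL/min. Everyone at or below that creatinine is excluded as printed, under any of the three cut-offs.

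**4. How many low-clearance patients the creatinine part still catches.** For a cut-off of 20 mL/min, the creatinine at which clearance reaches 20 was computed for 18 profiles (ages 40, 60 and 75; weights 50, 65 and 80 kg; both sexes). It lies below 3 mg/dL in 7 of them, from 1.92 (woman, 75 years, 50 kg) to 2.95 (woman, 40 years, 50 kg). In the other 11 it lies above 3 mg/dL, so creatinine excludes the patient before clearance falls to 20. With the 45 kg case added, the band missed runs from about 1.7 to 3 mg/dL, mainly in small or older patients.

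**The case against.** The strongest reply is that this is a slip in a condensed article that no clinician would follow. The criterion excludes people who have renal insufficiency, a patient with normal clearance does not have it, and the creatinine part shows the intended sense. Stage Two supports this: "A total number of 220 participants were randomly assigned", and it is implausible that all of them had clearance at or below 20 with creatinine at or below 3 mg/dL. The working documents may also be correct. All of this stands as an argument about consequences. It does not make the printed threshold right, and the article does not say which rule was used.

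A second reply concerns the connective. The instruction that one criterion suffices governs the listed criteria, not the items inside the bracket. That is fair, so the claim that the two eligible groups barely overlap is conditional on or. The line fails under and as well, in a different way.

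A third reply is that a missing word such as decline would explain both the sign and the percent. It is possible but less likely, because a fall of 20% is a far milder condition than the creatinine of 3 mg/dL beside it.

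A fourth is that the gap in safety is narrow. Under or, this also stands: the creatinine part still removes many severe cases, as the working shows.

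Two stronger readings should be set aside. A reader might infer that Stage Two enrolled the wrong population and that its ejection-fraction comparison is compromised; nothing in the article shows that. A reader might also infer that Stage Three will open at inexperienced sites. The text says only "In this stage, five or more centers will take part in the trial", and these could be among the seven Stage Two hospitals.

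**Conclusion.** The renal exclusion is wrong as written. Read as a level, its clearance part contradicts the creatinine part beside it, its unit has no reference, and the line carries into Stage Three. Under or, the likelier reading, it excludes patients with adequate clearance and misses those at or below 20 unless creatinine is above 3 mg/dL. Under and, it lets through the worst cases. A reversed sign is the most probable cause.

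The conclusion about direction rests on the printed text and the opposite behaviour of clearance and creatinine. The clearance values in mL/min rest on an assumed formula and assumed weights and serve only as illustration. The number of patients affected cannot be derived from the article. No effect on the ejection-fraction analysis, sample size, power or significance level is shown. This is a wording error in a safety threshold that should be corrected; it is not a flaw in the trial's inference.

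**What to change.** Before Stage Three opens, restate the criterion as: Ccr < 20 mL/min (or < 20% of normal, as the sponsor confirms) OR Scr > 3 mg/dL (265 μmol/L). The sponsor should confirm the unit and rule out that a decline was meant, and the connective should be explicit. Use the corrected wording in the preparation already planned in section 3.3: "Before the beginning of this stage, all investigators will be trained and tested according to conformance standard". For Stage Two, report which rule the sites applied.

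The cost is one line of protocol wording and one sentence in the Stage Two report. No new data are needed, because Table 5 already lists a renal function test at baseline, and no analysis changes.

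### The Stage Two sample size rests on unnamed pilot figures that are not credible as LVEF points and, as printed, do not give 98 per group, so power for the primary outcome is not shown

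*Protocol article*

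**What the plan says.** Section 3.1.2 (Stage Two), Sample Size, takes its inputs from a pilot: "The sample size calculation is based on prophase clinical study (31 cases, 13 in CHM group and 18 in placebo group"). In order, it prints:

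- the experimental-group SD, followed by the label of the next item: "25.84718, standard deviation of control group";
- the control-group SD: "32.54499, mean of experimental group";
- the experimental-group mean: "39.07692, mean of control group";
- the control-group mean and the allocation factor: "32.54499, and the number of control group (*c*) = 1".

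The result is "The estimated number of subjects in each group was 98.18012, and 196.36024 subjects are needed in two groups", raised for 10% dropout and set at 220 in total, 110 per group. The paragraph names no variable and no unit, and gives no numerical alpha or power. Alpha of 0.05 and two-sided testing appear only under Statistical Analysis.

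Under Outcome Measurements of the same stage: "The primary outcome measure was left ventricular ejection fraction (LVEF"). The inclusion criteria ask for "systolic volume of left ventricular increase with LVEF" of at most 40%. The Stage Three sample-size paragraph, by contrast, names LVEF as its basis. The Discussion reports that Stages One and Two are finished.

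**The concern.** A sample-size calculation supports a trial only if it concerns the primary outcome and its inputs lead to its answer. Here neither is shown.

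The printed spread is far wider than LVEF points would show in patients selected for LVEF of 40% or less. Separately, the control mean equals the control SD to five decimals, which is unlikely by chance and points to a transcription error in an input that drives the result.

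At stake is what a reader can say about the planned sensitivity of the LVEF comparison. Stage Three goes ahead only if CHM does better than placebo in Stage Two, so that decision rests on a comparison whose planned power for LVEF cannot be established from the article.

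**Working it through.** **Inputs.** From the Sample Size paragraph: Se = 25.84718, Sc = 32.54499, experimental mean 39.07692, control mean 32.54499, c = 1. From Statistical Analysis: alpha 0.05, two-sided. Power is not stated; 80% is assumed and 90% is shown as an alternative.

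**1. The plan's own figure.** The stated formula is n = (z_alpha + z_beta)² (1 + 1/c) σ² / δ², with σ² = (Se² + c·Sc²)/(1 + c).

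- σ² = (668.08 + 1059.18)/2 = 863.63, so σ = 29.39.
- δ = 39.07692 − 32.54499 = 6.53193, so δ² = 42.666.
- At 80% power, (1.960 + 0.842)² = 7.849, and n = 7.849 × 2 × 863.63 / 42.666 = 317.7, or 318 per group.
- At 90% power n is 425.4. With a one-sided test n is 250.3 (80%) or 346.7 (90%).

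The stated 98.18 is not reproduced. Nor is it by alpha of 0.10, 0.025 or 0.01, by power from 70% to 95%, by df-weighted pooling, or by either SD alone.

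**2. Power at the stated size, printed inputs.** Power ≈ Φ(√(n/2) × 6.53193/29.39 − 1.96). This is 34% at 98 per group and 38% at 110.

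**3. Which input is likely wrong.** Hold the other inputs, two-sided 0.05 and 80% power.

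- Solving for δ: √(7.849 × 2 × 863.63 / 98.18012) = 11.75, so the control mean would be 39.08 − 11.75 = 27.33. Because δ is squared, 50.83 also solves it. At 90% power the lower solution would be 25.48.
- Solving for the control SD instead: Se² + Sc² would have to be 98.18012 × 42.666 / 7.849 = 533.7, but Se² alone is 668.1. No control SD can repair the result.
- A hint: 39.07692 × 13 = 508.00, a whole number, but 32.54499 × 18 = 585.81 is not. A sum of 492 over 18 gives 27.333, and with rounded quantiles (1.96 + 0.84) n = 98.19, close to the stated value but not identical.

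This suggests that the control SD was copied over the control mean. It does not prove it.

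**4. Do the SDs fit LVEF points?** For n values between 0 and 40 with mean m, the largest sample SD is √(m(40 − m)·n/(n − 1)).

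| Group | n | Mean | Largest SD under the cap | Printed SD |
|---|---|---|---|---|
| CHM | 13 | 39.08 | 6.3 | 25.8 |
| Control, as printed | 18 | 32.54 | 16.0 | 32.5 |
| Control, reconstructed | 18 | 27.33 | 19.1 | 32.5 |

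Whatever the mean, the limit is about 20.8 (n = 13) or 20.6 (n = 18). Values after treatment are not capped at 40, and on a 0–100 scale SDs of 48 to 51 are arithmetically possible at the printed means. Even so, a normal distribution with the CHM figures has Φ(−39.08/25.85) = 6.5% below zero, and the reconstructed control figures have Φ(−27.33/32.54) = 20%. As a four-week change, a mean of +39 LVEF points is not credible. Correcting the control mean therefore leaves the mismatch in place.

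**5. What the achieved size means for LVEF.** The detectable difference at 80% power is 2.802 × SD × √(2/n): 0.40 SD at 98 per group and 0.38 SD at 110. The article gives no LVEF SD, so the SDs below are assumptions.

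| Assumed LVEF SD (points) | 98 per group | 110 per group |
|---|---|---|
| 6 | 2.4 | 2.3 |
| 8 | 3.2 | 3.0 |
| 10 | 4.0 | 3.8 |

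**The case against.** The strongest reply is that this is a reporting fault and not a design failure. The article condenses a fuller protocol that may name the pilot variable. Stage Two is finished, so nothing can be resized. Its result will be read from the planned 95% confidence intervals, which do not depend on pilot inputs. Stage Three is to be sized on LVEF from Stage Two, so the pilot figures do not carry over into that calculation. All of this stands, and it limits the consequence. It does not remove the point: the article prints a complete calculation to five decimals, omits what was measured, and reports a result that its inputs do not give.

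Three stronger readings are tempting but unsupported.

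- *The figures cannot be LVEF.* The 40% limit is Stage Two's entry criterion and applies at baseline. The pilot's entry criteria are not given, and a relative percentage change in LVEF is not excluded. Not credible as LVEF points is as far as the text goes.
- *The trial has no valid power.* Undocumented power is not absent power. Under the assumed SDs, 98 per group detects 2.4 to 4.0 points with 80% power, which may be adequate.
- *The trial is underpowered for 2 LVEF points, the δ printed for Stage Three.* There δ is subtracted from ε inside the squared denominator, so it acts as a margin. Stage Two sets no target difference on LVEF, and any such power would also rest on an assumed SD.

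**Conclusion.** The point holds in two parts.

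First, the Stage Two size is not tied to LVEF. The variable and unit are missing, and SDs of 25.8 and 32.5 are not credible as LVEF points in this population. Power for the primary outcome is therefore not shown. Whether it is adequate cannot be judged without an LVEF SD and a target difference.

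Second, and provable from the printed numbers, the inputs do not give the stated answer: about 318 per group against 98.18, with about 34% power at 98. The 318 and 34% assume two-sided 0.05, and the 318 also assumes 80% power. The control mean of about 27.33 is a reconstruction on the same assumptions. A reader might take it as established, but the documents do not settle it.

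**What to change.** In the Stage Two Sample Size paragraph:

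- name the pilot variable and its unit;
- correct the control mean from the pilot data and confirm that the formula then returns the stated n;
- state alpha, sidedness and power beside the calculation;
- keep n = 220, because Stage Two is completed, and give a justification on LVEF: the SD of LVEF or of its change, with its source, and the difference that 110 per group detects with 80% power (0.38 SD; 0.40 SD at 98 per group);
- if the pilot variable was not LVEF, disclose that the trial was sized on another variable and that power for LVEF was not planned.

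The cost is one rewritten paragraph and a look at the pilot records. The downside is that the stated power for LVEF may turn out less favourable than the present text implies.
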